## Abstract

**Background:**

Secondhand smoke exposure (SHSe) harms children’s health, yet effective interventions to reduce child SHSe in the home and car have proven difficult to operationalize in pediatric practice. A multilevel intervention combining pediatric healthcare providers’ advice with behavioral counseling and navigation to pharmacological cessation aids may improve SHSe control in pediatric populations.

**Methods/design:**

This trial uses a randomized, two-group design with three measurement periods: pre-intervention, end of treatment and 12-month follow-up. Smoking parents of children < 11-years-old are recruited from pediatric clinics. The clinic-level intervention includes integrating tobacco intervention guideline prompts into electronic health record screens. The prompts guide providers to ask all parents about child SHSe, advise about SHSe harms, and refer smokers to cessation resources. After receiving clinic intervention, eligible parents are randomized to receive: (a) a 3-month telephone-based behavioral counseling intervention designed to promote reduction in child SHSe, parent smoking cessation, and navigation to access nicotine replacement therapy or cessation medication or (b) an attention control nutrition education intervention. Healthcare providers and assessors are blind to group assignment. Cotinine is used to bioverify child SHSe (primary outcome) and parent quit status.

**Discussion:**

This study tests an innovative multilevel approach to reducing child SHSe. The approach is sustainable, because clinics can easily integrate the tobacco intervention prompts related to “ask, advise, and refer” guidelines into electronic health records and refer smokers to free evidence-based behavioral counseling interventions, such as state quitlines.

**Trial registration:**

NCT01745393 (clinicaltrials.gov).

## Background

Child secondhand smoke exposure (SHSe) is linked to asthma, respiratory illness, otitis, hospitalization rates, headaches, sudden infant death, and behavior problems
[1-4]. Because parental smoking is a primary source of SHSe in children, the American Academy of Pediatrics developed pediatric tobacco-intervention guidelines
[5] that address parental smoking. Pediatric healthcare visits provide a teachable moment to increase parents’ awareness of the adverse effects of SHSe on children and motivate them to protect children from SHSe
[6]. However, there are barriers to effective pediatric-clinic interventions. For example, competing demands, time limitations, and systems barriers may prohibit offering medications to address parents’ nicotine addiction or providing in-depth counseling and training in self-regulatory skills that can alter smoking behavior
[7,8]. The Kids Safe and Smokefree (KiSS) program addresses these limitations via a multilevel intervention model that integrates a pediatric clinic-level intervention with more intensive individual-level behavioral counseling and navigation to community-level services for nicotine dependence.

The KiSS clinic-level intervention focuses on improving the quality of clinic-delivered tobacco-related messages for parents. It emphasizes three elements, known as “Ask, Advise, and Refer” (AAR): Ask about child SHSe, Advise about the harms of SHSe and benefits of reducing SHSe, and Refer to cessation resources. The clinic AAR intervention can motivate and assist parents to take the initial actions to protect their children from SHSe. The KiSS behavioral health intervention then provides more intensive intervention that may be necessary to promote smoking behavior change. The behavioral intervention combines personalized, intensive family-centered counseling, smoking urge management and coping skills training and social support with community-level systems navigation to facilitate access to and effective use of no-cost nicotine replacement therapy and reimbursable cessation medication. The behavioral intervention includes a home visit to introduce intervention concepts and initiate skills training around reducing children’s SHSe in the home and car as a primary step toward preparing to quit smoking. The home is a critical target of intervention because restrictions on smoking across the U.S. do not typically extend to private homes and cars - contexts in which child SHSe is greatest. Weekly telephone counseling following the home visit initially emphasizes reducing child SHSe and then progresses to address smoking cessation and relapse prevention.

The design and sequencing of procedures in our trial were influenced in part by a pivotal review of smoking cessation interventions in medical practice. In that review, Kottke
[9] concluded that information to a smoker from one type of personnel (e.g., clinician) may potentiate information from another type of personnel (e.g., health counselor), and the number and duration of reinforcing sessions are related to cessation success. Kottke’s review focused on cessation, but we believe the same effects of multiple message sources and repeated “doses” of advice can be harnessed for SHSe reduction using an integrated multilevel, multimodal intervention. We will evaluate efficacy of the intervention in predominantly low-income, urban and minority communities with excess SHSe-related morbidity and mortality risk.

To date, most pediatric SHSe interventions adopt what Anderson
[10] has described as a single level of analysis--focusing either on environmental factors (e.g., smoke-free policies), social factors (e.g., pediatrician recommendation), or individual factors (e.g., motivation to change). The failure to develop a multilevel approach has impeded progress in the field because it is well established that smoking is multidetermined, and when an intervention targets a single level of a multidetermined behavior, that intervention provides insufficient elements to maintain healthy behavior change. For example, interventions that target one particular cause (e.g., limited knowledge about harm) might not address other relevant causes (e.g., nicotine addiction). Hence, a multilevel approach is likely to be more effective than a single-level approach.

The multilevel KiSS model follows recent recommendations to advance the science of health behavior change by testing a multilevel approach that addresses individual, group, and environmental influences simultaneously and over time. The model minimizes burden on clinicians, but the clinician still acts as a credible gateway to the more intensive intervention for smoking parents. The specific components of the clinic- and individual-level interventions are informed by the literature, including our preliminary studies and theory
[11-13]. For example, research links social support
[14], coping skills
[15], and self-efficacy
[16] to smoking behavior change. The KiSS interventions have elements shown to be associated with improved social support
[17], coping skills
[18], and self-efficacy
[19]. Other non-program factors, such as psychological symptoms
[20], nicotine dependence
[21], and presence of other smokers in home
[22], are known predictors of smoking outcomes and might moderate intervention efficacy.

### Aims and hypotheses

Aim 1: Test the primary hypothesis that an intervention integrating pediatric clinic-level quality improvement with individual-level behavioral counseling (AAR + BC) will be more effective in reducing children’s SHSe than a clinic-level quality improvement plus attention control intervention (AAR + AC). *Hypothesis:* Compared with children in the AAR + AC condition, those in the AAR + BC condition will have significantly greater reductions in SHSe from baseline to 3- and 12-month follow-up.

Aim 2: Test the secondary hypothesis that AAR + BC will be more effective in increasing parental quit rates than AAR + AC. *Hypothesis:* Compared with parents in the AAR + AC condition, parents in the AAR + BC condition will have a significantly greater smoking abstinence at 3- and 12-month follow-up.

Aim 3: Test hypotheses that social cognitive variables (social support, urge management coping skills, self-efficacy) will mediate effects of the AAR + BC intervention on outcomes. *Hypothesis*: Compared with parents in the AAR + AC condition, parents in the AAR + BC condition will report greater social support, coping skills, and self-efficacy related to smoking cessation and SHSe reduction from baseline to 3- and 12-month follow-up. In turn, these changes will account for between-group differences in child SHSe and parent cessation outcomes.

Aim 4: Explore factors that may affect outcomes and moderate intervention effects, including presence of other smokers at home, level of nicotine dependence, and depressive symptoms.

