### Procedures

Pediatric healthcare providers in partnering clinics will be trained to provide brief advice about child SHSe and to refer assenting parents to the KiSS research staff. The sampling frame includes any parent who meets the eligibility requirements following receipt of the clinic intervention and referral. Trained research assistants consent eligible participants and collect self-report data at baseline, 3-month end-of-treatment, and 12-month follow-up via structured telephone interviews. Interviewers are blind to participants’ intervention condition. Various procedures are used to reduce attrition, including reminder postcards and text messages, flexible scheduling, and financial retention incentives for completing different phases of the study.

Randomization is stratified by site and race using randomized permuted blocks of varying lengths. Because site and strata were not fixed design characteristics, the maximum number of allocations was generated within each combination of site and stratum. The project biostatistician provided the allocations to the data collection team in opaque sealed security envelopes. Randomization was seeded using values obtained from random.org. Participants are randomized prior to an orientation home visit that follows the baseline interview. Once a home visit appointment is confirmed, a research assistant takes the top envelope from the allocation pile to bring to the home visit. The envelope is opened immediately prior to the home visit to reveal the condition.

During the home visit, participants receive a binder with materials that are relevant to their assigned intervention condition and they provide a sample of the child’s urine for baseline cotinine assessment. The child’s urine is collected again at the 12-month follow-up. Parents who report quitting smoking at 12-month follow-up are asked to provide a biospecimen for cotinine verification of quit status.

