### Measures

#### Primary and secondary outcome variables

Participant self-report data is collected via telephone interviews. The primary dependent variable—child SHSe—will be measured in two ways. First, child cotinine will be collected in urine samples taken at baseline and the 12-month follow-up. Second, child SHSe will be measured by parental report of the number of cigarettes to which the child is exposed each day during the 7 days prior to all assessment periods
[28]. The secondary dependent variable—parent’s smoking cessation—will be assessed via parent-reported 7-day point prevalence abstinence for the 7 days prior to assessment at 3- and 12-month follow-up. The 12-month parent cessation report will be cotinine-verified.

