#### Covariates, mediators, and moderators

Three variables will be measured as potential covariates and possible moderators of intervention effects: nicotine dependence will be measured with the Fagerström Test for Nicotine Dependence
[29], symptoms of depression will be measured with the Center for Epidemiological Studies 10-item depression scale
[30], and a single self-report item will assess number of individuals who smoke daily in the home
[31]. Additional background factors, including demographics and smoking history variables will be assessed for possible association with outcomes. Three variables will be measured as potential intervention mediators: program support for smoking cessation will be measured with the short form of the Partner/Significant Other Interaction Questionnaire
[32] (adapted to focus on KiSS program support), coping skills will be measured with the Urge Management Coping Skills measure developed by the authors based on urge management coping strategies identified by O’Connell et al.
[33], and DiClemente’s Self-Efficacy measure
[34] will be used to measure people’s confidence in their ability to refrain from smoking in different situations.

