### Analytic plan

Child outcomes are continuous and the parent outcome is dichotomous. The predictor is intervention group (AAR + BC vs. AAR + AC). Additional covariates may include number of smokers in home, level of nicotine dependence, depressive symptoms, demographic, and smoking history. ANCOVA will be used for continuous outcomes and logistic regression will be used for the dichotomous outcome. Intention-to-treat analyses will be performed using multiple imputations with careful attention to missing data mechanisms. Potential covariates and effect modifiers will be considered as warranted. The influence of mediator variables, such as urge management coping skills, will be assessed using bootstrapping techniques that provide estimates of the indirect effects and test for their significance via confidence intervals
[35]. The SPSS macro developed by Preacher and Hayes to test multiple mediation models will be used to carry out the mediation analysis
[36].

Evidence for hypothesis 1 (child SHSe) will be provided by a significant negative coefficient for the indicator of AAR + BC participation. Evidence for hypothesis 2 (parent quit) will be provided by a significant positive coefficient for the indicator of AAR + BC participation. Evidence for hypothesis 3 (mediators) will be provided by significant associations between AAR + BC participation and social cognitive variables (positive) and between social cognitive variables and child SHSe (negative) and parent smoking (positive) outcomes. Evidence for hypothesis 4 (moderators) is exploratory; evidence for effect modification will be provided by significant coefficients associated with multiplicative composites between AAR + BC participation and potential moderating variables.

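### Aim 3 counts 12-month mediator change as explaining outcomes measured at that same 12-month assessment, with no time order required, so a consequence of quitting or lower exposure can be declared a mediator

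*Protocol article*

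**What the plan says.** **Hypothesis.** Aim 3 (Aims and hypotheses) proposes that "social cognitive variables (social support, urge management coping skills, self-efficacy) will mediate effects of the AAR + BC intervention on outcomes". The changes meant to do the explaining run from baseline to month 3 and from baseline to month 12, and the aim continues: "In turn, these changes will account for between-group differences in child SHSe and parent cessation outcomes". Change up to month 12 is thus named as explanatory, alongside change up to month 3.

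**Timing of measurement.** Under Procedures, research assistants "collect self-report data at baseline, 3-month end-of-treatment, and 12-month follow-up via structured telephone interviews". Under Primary and secondary outcome variables, "child cotinine will be collected in urine samples taken at baseline and the 12-month follow-up". Reported child exposure covers the 7 days before every assessment, and cessation is "parent-reported 7-day point prevalence abstinence for the 7 days prior to assessment at 3- and 12-month follow-up", with cotinine verification at 12 months. No outcome is scheduled after month 12.

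**Nature of a mediator.** The self-efficacy scale (Covariates, mediators, and moderators) is "used to measure people’s confidence in their ability to refrain from smoking in different situations".

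**Analysis.** The Analytic plan will use "bootstrapping techniques that provide estimates of the indirect effects and test for their significance via confidence intervals". It accepts as evidence for hypothesis 3 significant associations of arm with the social cognitive variables and of those variables with the outcomes. It states no lag and no pairing of visits.

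**The concern.** A mediator must change before the outcome it explains. A 12-month mediator has no later outcome left to explain, so it can only be paired with results from its own visit. For the self-reported outcomes the order in such a pair is even reversed: exposure and abstinence describe the preceding 7 days, while confidence is reported on the day.

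The reverse path is plausible on the protocol's own account. The behavioral counseling section describes a shaping approach in which progress on early goals sustains motivation and confidence. A parent who has stopped smoking, or stopped smoking indoors, may well report more confidence and better urge management because of that success.

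If the intervention works, anything that merely follows the outcome will then differ between arms and correlate with the outcome, which is the pattern the Analytic plan accepts as evidence. A correctly run bootstrap does not help, because it tests the size of an indirect effect and not its direction. At stake is the Discussion's promise that the mediator findings will show how the intervention works.

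**Working it through.** The protocol gives no figure on this point to reproduce. The check compares the stated timings and then illustrates the size.

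**1. Visit pairs that Aim 3 leaves open**

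| Mediator change to | Outcome at | Order |
|---|---|---|
| 3 months | 3 months (reported exposure, abstinence) | same visit |
| 3 months | 12 months (cotinine, reported exposure, verified abstinence) | mediator first |
| 12 months | 12 months | same visit |

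Only the middle row has the mediator first. The text does not single it out.

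**2. Same-visit bias by arithmetic**

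Inputs from Power analysis: 332 recruited, 30% attrition, so 332 × 0.70 ≈ 232 completers; d = .23 (the preliminary estimate) and d = .30 (top of the stated range). Assumed: the outcome-to-mediator correlation r, because the protocol gives none.

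Model with no mediation: Y = −d·T + e, and M = −r·Y + √(1−r²)·u, where e and u are independent with variance 1.

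- Arm on mediator: a = r·d.
- Mediator on outcome given arm: b = −r, since var(M given T) = r² + (1−r²) = 1.
- Indirect effect: a·b = −r²·d, which is a share r² of the total effect −d. For r = .3, .5 and .7 the spurious share is 9%, 25% and 49%.
- The signs (a positive, b negative) are the ones the Analytic plan asks for with child exposure.

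The standard error of a is 2/√232 = 0.131. The ratio of b to its standard error, r/√((1−r²)/229), is 4.8 or more, so b is almost always significant. The false-positive rate is then close to the chance that a is significant, P(|Z + a/0.131| > 1.96). For d = .30 and r = .5: a = 0.15, a/0.131 = 1.14, giving about 21%.

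**3. Same-visit bias by simulation**

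Same model, 95% percentile bootstrap with 500 resamples, 600 trials per cell (Monte Carlo standard error near a rate of 20%: √(0.2·0.8/600) ≈ 1.6 points).

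| d | r = .3 | r = .5 | r = .7 |
|---|---|---|---|
| .23, formula | 8.2% | 14.1% | 23.2% |
| .23, simulated | 8.5% | 16.5% | 20.5% |
| .30, formula | 10.5% | 20.8% | 35.9% |
| .30, simulated | 10.5% | 21.2% | 38.5% |

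The rate rises with the treatment effect.

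**4. Does a lag cure it?**

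Not alone. The 3-month mediator comes from the same interview as 3-month exposure and can react to it. Two simulations with 240 completers, a mediator that only reacts to same-visit exposure (reaction 0.3 to 0.5 SD per SD, assumed) and carry-over of exposure to month 12 gave these false-positive rates:

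| Setting | 12 with 12 | 3 with 12, unadjusted | 3 with 12, adjusted for 3-month exposure |
|---|---|---|---|
| First (arm effect on 3-month exposure 0.3 to 0.4 SD) | 13–40% | 7–36% | 0.1–0.3% |
| Second | 6–15% | 5–38% | under 1% |

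The settings differ in their assumptions, and the first has arm effects at or above the top of the protocol's range.

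**5. What the adjustment costs**

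In the second setting, with true mediation acting by month 3, the unadjusted lagged analysis detected it in 54–78% of trials and the adjusted one in about 5%. A separate simulation (arm effect on mediator 0.5, mediator effect on 3-month exposure 0.3 to 0.4, carry-over 0.5, all assumed) gave 51–81% against about 5%. With an added later direct mediator effect of 0.1, detection was 97% against 27%.

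**The case against.** **This is detail for the analysis plan.** The quoted sentence is a hypothesis. A condensed article commonly leaves visit pairing and covariates to the full protocol or analysis plan, which is not at hand. That stands for what is merely unstated, and nothing in the article forbids a lagged analysis. But the article itself names 12-month change as explanatory and sets an evidence rule without time order; an analysis plan that follows both carries the fault forward.

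**Stronger readings.** A reader might infer that the trial has committed to testing 12-month mediators against 12-month outcomes, or to explaining 3-month outcomes by 12-month change. The text proposes neither pairing. It permits the first and never mentions the second.

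**Order is not the whole problem.** This stands. The lagged pair alone still gave 5–38% false mediation, so it is not a full cure.

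**Adjustment can erase real mediation.** This stands too. Counseling runs for 12 weeks and addresses exposure first, so a genuine mechanism may have acted by month 3. Three-month exposure would then lie on the causal path, and adjusting for it cannot be the only test.

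**Not every mediator is equally exposed.** This stands. The support scale is adapted to support from the KiSS program, and there is less reason to expect quitting to raise it than to raise confidence or coping.

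**Conclusion.** The concern holds in a limited form. As written, Aim 3 and its evidence rule allow a consequence of quitting or lower exposure to be reported as a mechanism. With no true mediation and d = .23 to .30, same-visit false-positive rates were about 6% to 39% across simulations. The range rests on assumed reaction sizes and carry-over; it shows that the problem can be material and does not predict this trial's error rate.

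A reader might go further and conclude that the 3-month mediator with the 12-month outcome, adjusted for 3-month exposure, is the one correct analysis. The documents do not support that. Mediator and behavior at month 3 come from one interview, so their order within the first 3 months cannot be recovered, and the adjusted and unadjusted estimates fail in opposite directions. Nor does the point reach the treatment comparisons: Aims 1 and 2 are unaffected, and the Discussion itself calls the mediator aims secondary.

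**What to change.** Amend Aim 3 and the matching Analytic plan text as follows.

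- **Test.** Baseline-to-3-month change in each mediator, with 12-month child cotinine and 12-month verified abstinence as outcomes. Adjust for the baseline mediator and for the baseline outcome where one exists; it does for cotinine but not for abstinence, since all parents smoke daily at entry.
- **Bracketing.** Report the lagged indirect effect both without and with adjustment for 3-month behavior: reported exposure (there is no 3-month cotinine) or smoking status. State that the unadjusted estimate can be inflated by reverse causation and that the adjusted one removes mediation already completed by month 3.
- **Same-visit pairs.** Report 3 with 3 and 12 with 12 as associations, not as evidence of mechanism.

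Cost: wording and slightly more analysis. All the measurements are already scheduled. The price is a more cautious mechanistic conclusion, especially where the two bracketing estimates disagree.
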